### Number of patients needed

The sample size calculation is based on a two sided t-test for differences with respect to the primary endpoint. The data evaluation and comparison of seven patients operated on with the LVSS versus seven patients operated on with the conventional dissection technique showed a reduction of operating time of 40 minutes in the LVSS group. An evaluation of all pp-Whipple operations in 2010 (138 operations) showed a mean operating time of 300 min with a standard deviation of 66 minutes. If the difference in operating time is 40 minutes, there will be an 80% (1-β) chance that a trial involving 88 patients (44 per group) could detect a significant difference at an alpha level of 5%s (SAS 9.1 proc power). To compensate possible drop outs 14 patients (15%) more will be randomized. Therefore 102 patients (51 per group) will be included (Figure 1).

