**Examination of primary endpoints**:				
Mortality		X	X	X
Peri- and postoperative complications		X	X	X
Re-intervention			X	X
Intraoperative blood loss		X		
Hospital stay			X	
Reuptake			X	X
Time of anesthesia pre- and postoperative		X		
Intraoperative material consumption		X		
Local recurrence				X
Quality of life	X			X

Safety criteria AE, SAE (2.6)		X	X	X

* study-relevant past medical history, past surgical history

** height (cm), weight (kg), gender, Karnowsky-Index, medication of immunsuppresion, antibiotics, chemotherapy

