pp-Whipple specific complications	postoperative pancreatic fistula (POPF)	Drain output of any measurable volume of fluid on or after postoperative day 3 with an amylase content greater than 3 times the serum amylase activity. Three different grades of POPF (grades A, B, C) are defined according to the clinical impact on the patient's hospital course [22]
	
	Intraabdominal abscess	Intraabdominal collection of purulent or infected fluids (positiv bacterial culture) requiring radiological (puncture or drainage of purulent fluid) or surgical intervention (re-operation)
	
	anastomotic leakage of choledochojejunostomy	Bilirubin-rich (more than 5000 units) drainage fluid of more than 50 ml per day on or after the 10th postoperative day OR Mentioned in re-operation report
	
	anastomotic leakage of gastrojejunostomy	Radiological findings correlating to gastrojejunostomy insufficiency (e.g. CT with contrast medium withdrawal) OR Mentioned in re-operation report

Further secondary endpoints		Definition

Re-intervention	operational	Reoperation due to any cause

	interventional	Interventional haemostasis or drainages due to any cause

Intraoperative blood loss		Mentioned in operation report

Hospital stay		Time of admission to discharge

Re-hospitalization-rate		Re- hospilization within 30 days after surgery due to any cause

Duration of anesthesia		Mentioned in anesthesia report

Intraoperative material consumption		All materials, which are necessary for surgery

Material costs		Costs, which occurs due to the material consumption during the surgery

Overall costs		Costs include expenditure for personnel and use of operating room as well as for material consumption

Local recurrence of disease		Radiological (ultrasound, CT) findings positive for recurrence of disease

Quality of life		EORTC QLQ-C30, EORTC QLQ PAN26 and special questionnaire of the European Pancreas Center Heidelberg on day 30 (±10days), 90 (±10 days), 180 (±10 days), 1 year (± 1 month), 1,5 years (± 1 month), 2 years (± 1 month), 2,5 years (± 1 month) and 3 years (± 1 month)

Mortality rate		Death to any course until year 3 after operation

Assessment:

1. Perioperative complications of the pp-Whipple procedure will be recorded on the day of operation by an independent study nurse.

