## Analysis

Comparisons will be made of the primary endpoints of both intervention groups for all randomized patients who underwent surgery involving the pp-Whipple procedure. Patients will be analysed as randomized applying the ITT principle [18]. In addition, a per-protocol analysis will be performed, including patients who are strictly treated according to the study protocol.

The outcome measures of the primary endpoint will be tested confirmatory applying an analysis of covariance with treatment as factor and age and BMI as continuous covariates.

Secondary endpoints will be analysed in a descriptive manner. Graphically methods will be used by means of box- and scatter- plots. For all continuous secondary endpoints a t-test will be applied, possible differences of categorical secondary endpoints will be analysed using chi-square tests. All p-values will be used as descriptive statistics only without any confirmatory value.

The secondary endpoint Quality of Life (EORTC QLQ-C30, EORTC QLQ PAN26) will be anlysed by an application of analysis of covariance that adjusts for age and EORTC QLQ-C30, EORTC QLQ PAN26 before surgery.

The following procedure will be applied for missing data:

If at least half of the items from the scale have been answered, the missing items are replaced by the average of those items that are not missing (calculated average rounded to the nearest integer). If less than half of the items from the scale have been answered, the scale is set to missing [19].

If it is evident that missing items or missing scales are related to a worsening in physical functioning, the missing values are replaced by the worst value measured in the respective intervention group at the respective time point.

The average EORTC QLQ-C30, EORTC QLQ PAN26 score can be calculated, if at least one measurement at day 30 (±10days), 90 (±10 days), 180 (±10 days), 1 year (± 1 month), 1,5 years (± 1 month), 2 years (± 1 month), 2,5 years (± 1 month) or 3 years (± 1 month) after surgery is available; if no measurement of the EORTC QLQ-C30 or EORTC QLQ PAN26 after surgery is available, the secondary endpoint is missing and the patient is therefore not included into the analysis.

All statistical analyses will be performed using SAS^® ^software, Version 9.1 (or higher) of the SAS System for Unix (SAS Institute Inc., Cary, NC, USA).

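### Filling missing quality-of-life values with the worst value of the patient's own arm inflates chance differences between arms, and Table 1 marks no quality-of-life assessment at the day-30 visit that is to be analysed

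*Protocol article*

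**What the plan says.** All places are in the protocol article.

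- **Imputation (Analysis).** When missing items or scales are evidently linked to worse physical functioning, "the missing values are replaced by the worst value measured in the respective intervention group at the respective time point".
- **Summary over visits (Analysis).** The average post-operative score "can be calculated, if at least one measurement at day 30" or at any of seven later time points up to 3 years exists. A patient with no post-operative measurement is left out.
- **Model (Analysis).** Analysis of covariance adjusted for age and the pre-operative score. Secondary p-values are descriptive.
- **Time points (Table 2).** The two EORTC questionnaires are to be completed with the "special questionnaire of the European Pancreas Center Heidelberg on day 30 (±10days") and at the later time points.
- **Schedule (Table 1).** Visit 1 is a telephone contact on day 30. The row "Quality of life" is marked at screening and at visits 2-8, and is empty at visit 1.
- **Follow-up text (Secondary endpoints, Assessment, item 2).** Visit 1 is a telephone interview on complications. The EORTC questionnaires are named with the aftercare visits from month 3 to month 36.

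**The concern.** The worst observed score in an arm is a single extreme, and extremes are unstable. Two arms with the same quality of life will usually have different minima. The rule gives that accidental difference to every imputed patient in the arm, and the analysis then treats these identical values as independent observations. The printed standard error is too small for the real variability of the arm difference, so confidence intervals are too narrow and descriptive p-values too small.

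Two further matters bear on the same endpoint. An average over whatever visits exist mixes quality of life with length of follow-up. And the article disagrees with itself on whether quality of life is measured at day 30, the first of the eight time points that it analyses.

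**Working it through.** **1. The article's own figure.** The quality-of-life rules carry no figure. The only design figure is the sample size: "The sample size calculation is based on a two sided t-test for differences with respect to the primary endpoint", with a difference of 40 min, SD 66 min, 5% alpha and 80% power. The normal approximation gives 2 × (1.96 + 0.84)² × 66² / 40² = 42.7, so 43 per arm. The exact t-test gives 43.7, so 44 per arm with 80.3% power. The stated 44 per group is reproduced and is used below as the arm size.

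**2. What the rule does.** Let a share p of each arm be imputed, with observed means m1, m2 and arm-specific worst values W1, W2. The arm difference is

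(1 − p)(m1 − m2) + p(W1 − W2).

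The second term averages zero when the arms are alike, so there is no directional bias. Its variance, however, is not in the usual standard error. Example: minima of 0 and 25 with p = 20% give a gap of 0.20 × 25 = 5 points from the rule alone; with p = 10%, 2.5 points. If W1 = W2 the term vanishes.

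**3. Size under no true difference.** Assumptions that are not in the article: a 0-100 scale with higher better, mean 60 and SD 22, and a random number of patients imputed, unrelated to their score. One visit, unadjusted t-test, 44 per arm, 4,000 replicates.

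| Imputed in each arm | Own-arm worst: SD of difference | Own-arm worst: rejection | Pooled worst: SD of difference | Pooled worst: rejection |
|---|---|---|---|---|
| 10% | 5.7 | 7.0% | 5.5 | 5.0% |
| 20% | 6.9 | 10.3% | 6.1 | 5.2% |
| 30% | 7.8 | 14.8% | 6.3 | 5.1% |

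A second run of the own-arm rule gave 7.0%, 10.7% and 14.4%. The Monte Carlo error near 15% is √(0.15 × 0.85 / 4,000) = 0.6 percentage points, so the runs agree. With mean 70 and SD 15 the own-arm rates are 7.3%, 10.7% and 16.6%. A fixed scale minimum in both arms gives 4.5-5.2%.

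**4. Unequal missingness.** With 10% imputed in one arm and 20% in the other, the mean shift is 3.1-4.4 points under the own-arm rule and 3.7-6.9 points under a common value. Check for a scale minimum of 0 and mean 60: (0.20 − 0.10) × (60 − 0) = 6.0, against 6.04 simulated. A common value therefore does not solve this case.

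**5. Average over available visits.** Assumed recovery from 45 at day 30 to 65 from 1 year, no treatment effect, 44 per arm. Equal dropout per visit (10% or 20% in both arms) gives a difference of about 0 and 5% rejection. Dropout of 10% against 20% gives 2.8 points and 10.5%; 10% against 30% gives 5.1 points and 25%. The contrast is distorted only when visit availability differs between arms.

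**6. Day 30, side by side.** Table 2 and the Analysis section list day 30 as a quality-of-life time point. Table 1 leaves the cell for visit 1 empty. Neighbouring rows such as mortality do carry a mark at visit 1, so a shifted column is unlikely. Item 2 of the Assessment text agrees with Table 1.

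**The case against.** **The effect depends on assumptions.** This is true. If exactly the same number is imputed in both arms, the own-arm rule rejects in only about 3.5% of trials at 10% imputed and 5% at 20%, rising to 8-9% at 30%. That set-up makes the t-test conservative, because a common value then rejects in under 2%; the own-arm rule is still the worse of the two. An eight-visit average with baseline-adjusted covariance analysis (assumed within-patient correlation 0.5) rejects in 5.1%, 7.2% and 7.7% at 10%, 20% and 30% imputed if the same patients are always missing. If missingness is independent by visit, the rates are 6.9%, 12.7% and 16.1%. The mechanism stands, but its size is uncertain.

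**The rule is conditional and the endpoint descriptive.** Both are correct. The rule covers only missingness evidently tied to physical decline, and nothing extends it to all missing data or to deaths. A descriptive estimate with too narrow an interval still misleads, but no confirmatory claim rests on it.

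**Stronger readings that the article does not support.**
- A reader might infer that the imputation favours one arm. With equal missingness it does not.
- A reader might compare a patient measured only at day 30 with one measured at every visit: under an assumed profile of 45, 58, 65 and then 68, this is 45 against 63.5. That is a gap between two hypothetical patients, not between arms.
- A reader might infer that the day-30 visit is unscheduled, or that day-30 quality of life will not be collected. The visit is in Table 1, and Table 2 says that the questionnaires are completed then. What is established is a contradiction.

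**Conclusion.** The point holds in limited form. The own-arm worst-value rule is stated in the article and gives wrong error rates: about 7%, 11% and 14% instead of 5% at 10%, 20% and 30% imputed. These rates rest on 44 per arm, one visit, an unadjusted t-test, an assumed mean of 60 and SD of 22, and a random number imputed equally often in both arms. The article gives neither the score distribution nor the missingness rate. The defect is excess variance, not directional bias.

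The any-visit average is a conditional weakness: it matters if visit availability differs between arms and scores change over time. The day-30 conflict is definite and needs no assumption.

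The consequence is confined to a secondary endpoint with descriptive p-values. Operating time and its sample size are untouched.

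**What to change.** 1. In the Analysis section, replace the own-arm worst value by one value common to both arms: the pooled worst value at that time point, or the worst possible scale score. Label the result a sensitivity analysis and set it beside an analysis of the observed scheduled visits, since a common value leaves unequal missingness unresolved.
2. As a supplement to the any-visit average, report baseline-adjusted arm differences by scheduled visit, for example from a repeated-measures model. This is a reasonable addition rather than a necessary correction, and it does not by itself settle how deaths are handled.
3. Reconcile day 30: either mark quality of life at visit 1 in Table 1 and name the questionnaires in the follow-up text, or delete day 30 from Table 2 and from the Analysis section.

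Items 1 and 2 cost a few sentences of analysis text. Item 3 costs one table entry and one more questionnaire round for patients, or a deletion. Neither the sample size nor the primary analysis changes.

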## Study organization

After approval of the protocol by the local ethics committee of the University of Heidelberg, the trial was internationally registered at Germanctr.de (DRKS00000166). All patients scheduled for a pp-Whipple procedure in the Department of General, Visceral and Transplantation Surgery, University Hospital of Heidelberg, will be referred to and screened by members of the Clinical Study Center Surgery (KSC). The results of the screening will be recorded in the screening-log.

Approximately 300 patients per year undergo a pp-Whipple procedure in the Department of General, Visceral and Transplantation Surgery, University Hospital of Heidelberg. The estimated time frame to randomize 102 patients will be approximately 15 months.

The sponsor of the DISSECT trial is Covidien GmbH (Germany).

The independent data management and statistical analysis will be carried out by the Institute of Medical Biometry and Informatics (IMBI) of the University of Heidelberg according to a prespecified Statistical Analysis Plan. It controls the completeness and correctness of the CRF as well as the administration.

The principal investigator has the right to terminate the trial and to remove all trial material from the trial centre at any time in consultation with the Clinical Study Team Leader and the Biostatistician. Reasons that may require a termination of the trial include the following:

• The incidence or severity of adverse events in the trial indicates a potential health hazard caused by the study treatment

• It appears that the patient's enrolment is unsatisfactory with respect to quality or quantity or data recording is severely inaccurate or incomplete

• External evidence that renders the necessity to terminate the trial

## Abbreviations

IMBI: Institute for Medical Biometry and Informatics; c-Whipple: classic-Whipple; pp-Whipple: pylorus-preserving-Whipple; LVSS: LigaSure™ Vessel Sealing System; HF: high frequency; SAS: Statistical Analysis Systems; CRF: case report file; RITA: Real Time Interactive Applications; KSC: Clinical Study Venter Surgery; PPW: pylorus-preserving Whipple; POPF: postoperative pancreatic fistula; EORTC: European Organisation for Research and Treatment of Cancer; QLQ-C30: Quality of Life Questionnaire-Core 30; QLQ-PAN26: Quality of Life Questionnaire- Pancreatic Cancer Module 26; CT: computed tomography; MRT: magnetic resonance tomography; AEs: adverse events; SAEs: serious adverse events; ITT: intention to treat; CDC: Centers for Disease Control and Prevention; DGE: delayed gastric emptying; ISGPS: International Study group of Pancreatic Surgery.
